### Standardisation across the two sites

All clinical test procedures will be piloted between sites to ensure standardisation. Inter-rater reliability of range of motion using the inclinometer for nerve mechanical sensitivity testing will be performed. The German Network of Neuropathic Pain QST protocol has shown to have substantial inter-rater and inter-centre reliability.^56 57^ The same MR scanners and coils are available at both sites so that settings will be identical. Any differences between sites will be adjusted at the analysis stage by comparing healthy controls at both sites.

Several quality control checks will be performed including checking of data entry (exchange of data sets between sites) and a comparison of healthy control data obtained at both sites.

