### Study design

This is a prospective cohort study at two centres. A total of 115 participants will be recruited following a whiplash injury within 1 month of their original injury. We will also recruit 34 healthy proportionally age-matched and gender-matched control participants. People with acute WAD2 and healthy control participants will attend a baseline appointment. In addition to MRI, a detailed musculoskeletal assessment will be performed, as well as tests of nerve trunk mechanical sensitivity and quantitative sensory testing (QST). A blood sample will be taken and analysed for levels of inflammatory markers. Participants will also be asked to complete a series of validated questionnaires to assess neuropathic symptoms, functional deficits, quality of life and psychological factors. For the substudy, skin biopsies from the index finger and ankle will also be taken. At 6 months, the Neck Disability Index and a self-rated global recovery question will be used to determine recovery. A sequential sample of patients will be invited to attend a follow-up appointment during which the same detailed assessments will be repeated (figure 1).

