### Sample size calculation

Mean nerve signal intensity ratio data from our previous cross-sectional study of 13 controls and 9 participants with chronic WAD2 were analysed using a linear mixed model.^9^ The observed difference in means between controls and WAD2 participants was 0.0600 (SE=0.0315) for the C5–C8 roots of the brachial plexus, which was statistically significant; age was not a statistically significant covariate. The intraclass correlation coefficient of the nerve signal ratio was estimated to be 0.45. Assuming that there are eight assessments per participant (two sides × four roots), a SD of 0.1, intraclass correlation coefficient of 0.45 and a ratio of 3 participants with whiplash to one healthy control, the study would require 48 participants with whiplash and 16 controls to detect an effect estimate of 0.06 for the mean nerve signal intensity difference (80% power, 5% significance). Since in the acute stage it is estimated that only 50% of the participants with whiplash will develop chronicity,^51^ we will need to image 96 participants with whiplash and 32 controls for objective 1 (difference in neuroinflammation in the acute stage). Based on ~48 participants who have not recovered at 6 months, we would be able to fit a logistic regression model with 5–10 predictor variables for objective 2 (predictive factors of chronicity).

For objective 3 (development of neuroinflammation over time), we will ask 25 participants who have recovered and 25 participants who have not recovered to return at 6 months, which will enable an effect size of 0.9 to be detected using analysis of covariance, with 95% power for 5% significance. This value assumes that the correlation between the acute and chronic measurements is 0.5.

For objective 4 (validity of low cost tests of neuroinflammation), with nine independent variables, a rule of thumb for a multiple linear regression (ie, 10 participants per additional variable) implies that data from 90 participants with whiplash should be adequate to explore this.^52^

For the substudy, 68 participants with whiplash and 34 healthy controls (80% power, 5% significance, 0.53 effect size, one-tailed test) would allow the detection of a 20% smaller difference in intraepidermal nerve fibre density in the acute stage compared with healthy controls based on our previous cohort of patients with chronic WAD2.^53^

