Previous longitudinal studies on WAD2 have demonstrated a <15% dropout rate over 6 months,^54 55^ and therefore we will recruit 115 participants with acute WAD2 and 34 healthy control participants.

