### Statistical analysis

Data will be exported to Stata (V.17, StataCorp, Texas, USA) for analysis. The distribution of the data will be checked for normality, and parametric, or non-parametric methods will be used as appropriate. Participants’ characteristics will be described at all time points.

For objective 1, regression analysis, or non-parametric tests, will be used as appropriate to identify differences in MRI parameters (T2-weighted STIR 4 nerve roots per side, nerve morphology and DTI parameters) and clinical tests (eg, neuropathic pain scores, tests of nerve mechanosensitivity, QST and serum inflammatory markers) between participants with acute WAD2 and age/gender-matched controls. Regression analysis will be used to assess associations with age and height.

For objective 2, recovery of participants with WAD2 will be determined at 6 months with the Neck Disability Index and a global recovery question. The analysis will be conducted with three models using different predictors measured in the acute stage: (a) MRI parameters of neuroinflammation, (b) clinical parameters that reflect neuroinflammation and (c) the addition of MRI to clinical parameters to determine whether this improves predictive strength. The dependence between MRI and clinical assessments will be investigated and composite measures added to the model. In addition, a linear regression will be performed of Neck Disability Index scores on measures of neuroinflammation.

For objective 3, mixed effects modelling will be used to compare MRI and clinical measures between recovered and non-recovered participants with WAD2 over time.

For objective 4, multivariable regression will be used to investigate the relationship of each MRI variable with the clinical parameters of neuroinflammation. In addition, a regression analysis will be performed between clinical measures of neuroinflammation and MRI parameters.

For the substudy, independent t-tests or non-parametric alternatives will be used to compare dermal and intraepidermal nerve fibre density in skin biopsies in patients in the acute phase after whiplash injury with healthy controls. Separate regression models will be used to investigate whether changes in nerve fibre density in the acute stage predict pain persistence at 6 months.

Data reduction techniques (eg, principal components analysis) may be used prior to regression modelling.

Missing data will be managed with multiple imputation strategies.

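### Adjusting for site from the 34 healthy controls alone is imprecise and cannot reach patient-only measures, and the substudy test and any simple rank test leave out the matching factors

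*Protocol article*

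**What the plan says.** Under Study design the article states: "This is a prospective cohort study at two centres". The controls are described there as "34 healthy proportionally age-matched and gender-matched control participants". The planned numbers, at the end of the Sample size calculation, are: "we will recruit 115 participants with acute WAD2 and 34 healthy control participants".

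The section on standardisation across the two sites gives the only analytic remedy for site effects: "Any differences between sites will be adjusted at the analysis stage by comparing healthy controls at both sites". The same section also lists a comparison of control data between sites as a quality check.

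Under Statistical analysis, the objective 1 method is that "regression analysis, or non-parametric tests, will be used as appropriate to identify differences in MRI parameters" and clinical tests between patients and controls. Age and height come in as follows: "Regression analysis will be used to assess associations with age and height". Gender appears only in the description of the controls. For the substudy, "independent t-tests or non-parametric alternatives will be used to compare dermal and intraepidermal nerve fibre density". No model for any objective is said to contain site.

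**The concern.** The article commits to a specific method, and that method estimates the site offset from the smaller group and sets aside what 115 patients could say about it. It also needs the offset in healthy people to apply unchanged to injured people.

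For some measures it has nothing to work on. Table 1 assigns the pain scale, painDETECT, the Neck Disability Index and the psychological scales to whiplash participants only. A neurodynamic test counts as positive when it brings on the participant's own symptoms, so symptom-free controls say little about how the two sites score patients.

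A poorly estimated offset enters objective 1 to the extent that the site mix differs between patients and controls. It enters objectives 2 and 4 as noise or confounding in the predictors. Separately, controls are matched proportionally on age and gender, but a two-sample t-test or an ordinary rank test carries neither factor, nor site. An ordinary rank test on root-level T2 would also not deal with the eight correlated values per participant that the sample size assumes.

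**Working it through.** **Inputs.** From the Sample size calculation: "a SD of 0.1, intraclass correlation coefficient of 0.45 and a ratio of 3 participants with whiplash to one healthy control"; eight root values per participant; target difference 0.06; 80% power; 5% significance (taken as two-sided). Planned numbers are 115 patients and 34 controls. The split of either group by site is not given, so a range is shown.

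**Step 1: reproduce the plan's figure.**
- Variance of a participant mean = 0.1² × (1 + 7 × 0.45)/8 = 0.0051875, so SD = 0.0720.
- Controls needed at 3:1 = (1 + 1/3) × [0.0720 × (1.96 + 0.84)/0.06]² = 15.08, rounded up to 16, with 48 patients.
- This matches the stated 48 and 16, so 0.0720 is the plan's own working SD.

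**Step 2: precision of the site offset, even split assumed.**
- From controls only: √[0.0051875 × (1/17 + 1/17)] = 0.0247. The 95% half-width is 1.96 × 0.0247 = 0.048.
- From a site term across all 149: √[0.0051875 × 4/149] = 0.0118.
- Variance ratio: 149/34 = 4.4.

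**Step 3: what reaches objective 1.** Let p be the share of controls, and q the share of patients, at the same site.
- Var(group difference) = 0.0051875 × (1/115 + 1/34) + (q − p)² × Var(site offset).
- The first term is 0.0001977 (SE 0.0141).
- For the control-based rule, Var(site offset) = 0.0051875 × [1/(34p) + 1/(34(1 − p))].
- For a site covariate, that control estimate and the corresponding patient estimate are combined by inverse variance.
- The last column is 2 × [1 − Φ(1.96 × √(0.0001977/Var))], where Var is the control-based variance. It applies only if the estimated offset is subtracted as though it were known.

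| p / q | SE, control-based | SE, site covariate | SE increase | Type I error if offset taken as known |
|---|---|---|---|---|
| 50/50 | 0.0141 | 0.0141 | 0% | 5.0% |
| 50/70 | 0.0149 | 0.0143 | 4% | 6.4% |
| 50/80 | 0.0159 | 0.0147 | 8% | 8.3% |
| 30/70 | 0.0177 | 0.0150 | 18% | 12.0% |

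Worked example at 50/70, control-based: 0.0001977 + 0.2² × 0.0247² = 0.0002221, square root 0.0149.

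**Step 4: patient-only objectives.** Take an illustrative offset of 0.03 and an even split.
- Left uncorrected, it adds 0.25 × 0.03² = 0.000225 to a between-participant variance of 0.0051875, about 4%. A regression slope on that MRI measure would be attenuated by about 4% if site is unrelated to outcome.
- Correcting with an offset whose SE is 0.0247 adds on average 0.25 × 0.0247² = 0.000153, about 3%.

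**Step 5: age and gender.** The document gives no effect of either on any outcome, except that age was not statistically significant in the pilot model. No figure can be computed.

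**The case against.** The strongest reply is that a journal article need not list covariates. That stands for the objective 1 regression: the text does not say that age, gender or site are left out, so one cannot infer that matching is ignored throughout. It is certain only for the substudy t-test or its non-parametric alternative and for an ordinary rank test in objective 1. A stratified rank test such as van Elteren's could take site as a stratum, but none is named. The reply does not cover the site rule, which the article spells out.

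Two stronger readings of that rule are tempting. One is that the offset will be treated as known. The other is that adjustment will follow only if the controls show a difference; with 17 per site, power to show an offset of 0.03 would be 23%, against 72% with all 149. The sentence supports neither mechanism, so the inflated type I error is conditional and the 23% is not a property of the plan.

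Nor does an offset SE of 0.0247 against a target of 0.06 mean that objective 1 is swamped. The offset cancels at equal site shares. In objective 3, a constant offset cancels from within-person change, provided people return to the same site. The plan also limits offsets at source, with the same scanner model and coils, T2 normalised to adjacent tissue, and piloted procedures.

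The rule has a rationale too. Patients come from different catchments, and healthy controls help separate measurement differences from case mix, whereas a site term absorbs both. The two standard errors may therefore not describe quite the same quantity. This makes the control comparison a useful check. It does not make it the better adjustment, because carrying its offset over to patients is itself an assumption, and a site term fitted in patients does not need it.

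On patient-only measures, the abstract can be read as having controls complete questionnaires, and objective 1 lists neuropathic pain scores among its comparisons. Table 1 and the Questionnaires section assign them to patients.

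**Conclusion.** The point holds in a limited form. As a stated method, the site rule is inefficient: offset variance is 4.4 times that of a site term, assuming even splits and the plan's SD and intraclass correlation in both groups. It depends on control offsets transferring to patients and, on Table 1, cannot adjust measures collected only in patients.

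The harm to objective 1 ranges from none to an 18% larger standard error over the imbalances examined, and the actual imbalance is not documented. For patient-only regressions on T2 signal, the illustrative attenuation is a few per cent.

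The substudy comparison leaves out age and gender despite matching on them, as would any simple rank test in objective 1. The size and consequence of that cannot be determined from the document, and a reader should not infer that the standard errors are materially wrong. The case for change is that a better method is available at little cost, not that the planned results would be invalid.

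**What to change.** Replace the site rule with a statement that site is a covariate in the regression and mixed models, and keep the comparison of controls between sites as the quality check already listed.

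For the patient-control comparisons, include age and gender as well as site. In the substudy, use a regression in place of the t-test or rank test, with robust or bootstrap standard errors if the residuals call for them. Analyse root-level T2 by a linear mixed model with a participant random intercept, in line with the pilot analysis and the sample size assumption.

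This changes wording only and needs no new data. It uses a few degrees of freedom, which is minor with 149 participants but not free in objective 2. With about 48 events and 5–10 predictors there are 48/5 = 9.6 to 48/10 = 4.8 events per predictor. Adding site on top gives 48/6 = 8.0 to 48/11 = 4.4; adding site, age and gender gives 48/8 = 6.0 to 48/13 = 3.7. The site term should therefore count within the 5–10 limit. Age and gender need not be forced into the patient-only models on matching grounds, since matching concerns only the comparison with controls.

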### Data sharing

Project data will be made available via open access publications, as well as the study webpage and the Universities of Sussex and Oxford repository, which are openly accessible. A statement will be placed on the study webpage and publications asking new users to contact the principal investigator if they wish to have access to the original data set. Anonymised data will be made accessible on reasonable request once published or following completion of the study, adhering to data protection regulation and the Human Tissue Act (2004).

### Current status of the study

Recruitment of participants to the study commenced in July 2021 and will continue until early summer 2023. The study is expected to be completed by August 2024.

## Ethics and dissemination

The study has received sponsorship from the University of Sussex and ethical approval from the London-Brighton and Sussex Research Ethics Committee (20/PR/0625) and South Central—Oxford C Ethics Committee (18/SC/0263). The study is sponsored by University of Sussex which provides oversight for the totality of research sponsored by the University throughout the life-cycle of the study. Additionally, the study is independently reviewed annually by the funding body. Any protocol amendments will be scrutinised and approved by both the study sponsor and the Health Research Authority and changes to the protocol amended at ClinicalTrials.gov.

The results of this study should be of great interest to people after whiplash injury, clinicians, researchers, legal and insurance companies and policymakers. Dissemination via a multitude of platforms is therefore necessary to enhance its reach. We plan to publish traditionally in open access peer-reviewed journals as well as presenting at national and international conferences. In addition, dissemination will occur via social media outlets. Patient and clinician information resources such as infographics will be produced and disseminated. Additionally, the patient partner group will support best strategies for dissemination to reach patient groups as well as policy makers. Local presentations to stakeholder groups such as patient groups, health authorities and professional bodies will be given.
